	Time-to-imaging decision	Compare time from triage to CT decision between arms.	Evaluate whether biomarker access accelerates or delays decision-making.
	Disposition flow	Evaluate differences in ED-to-disposition pathways with vs. without biomarker data.	ED throughput times, floor/ICU admissions.
Secondary (validation) full cohort as single arm	Diagnostic accuracy	Determine sensitivity, specificity, NPV, and PPV of biomarkers vs. CT findings for intracranial lesions.	Biomarker levels vs. CT results.
	Kinetic profiling	Evaluate the kinetics and temporal profile of GFAP/UCH-L1 across 0, 8, 16, and 24 h.	Serial biomarker levels, time-to-peak and decay curves.
	Predictive modeling	Build multivariable models using biomarkers and clinical data to predict imaging-positive patients.	ROC curves, AUC, logistic regression outputs.
	Triage integration	Assess biomarker utility in supplementing current BIG criteria for TBI triage.	Sensitivity/specificity when combined with BIG criteria.
	Outcome prediction	Evaluate whether biomarker levels predict functional outcomes or neurologic decline.	Correlation with GOSE score, readmission, or symptom progression.
Secondary (implementation) only published cohort	Implementation feasibility	Assess provider adherence to biomarker interpretation guidelines in the biomarker-published arm.	Understand clinical adoption barriers and fidelity to protocol including provider and patient variables
	Patient perception	Evaluate patient understanding and satisfaction with biomarker-driven decision-making.	Gain insights into trust and acceptance of non-imaging diagnostics.

TBI, traumatic brain injury; CT, computed tomography; ED, emergency department; LOS, length of stay; ICEA, incremental cost-effectiveness analysis; GCS, Glasgow Coma Scale; GOS, Glasgow Outcome Scale; GOSE, Glasgow Outcome Scale-Extended; ICU, intensive care unit; NPV, Negative predictive value; PPV, Positive predictive value; ROC, Receiver Operating Characteristic; AUC, Area under the curve; BIG, Brain Injury Guidelines.

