### Pre-randomization procedures

Screening of eligible patients will be performed by study personnel via real-time tracking of ED dashboard for new admissions or transfers. Triage notes and evaluations will be reviewed for primary eligibility based on age, type of injury, reported GCS, timing of injury and whether existing head imaging is present. If subjects pass screening, they will be approached for review of detailed inclusion and exclusion criteria and for consent process. Written informed consent (from the patient or legally authorized representative) is obtained before any study-specific activities. Providers are notified about patient enrollment and requested to hold off on obtaining CT head imaging until randomization and biomarker data is available. Randomization variables will then be obtained, and subjects will be randomized using an automated algorithm implemented in RedCap into published or blinded biomarker groups.

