### Procedures for blinded biomarker arm

For the blinded arm, no further changes are requested from the provider, and a venous blood sample is then collected for point-of-care GFAP and UCH-L1 measurement using the i-STAT TBI cartridge; results are withheld from clinicians. The patient will then be followed up during the hospitalization for reviewing provider decisions, imaging data, clinical outcomes, and disposition as listed in the outcome section.

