### Procedures for the published biomarker arm

For the published arm, providers are requested to pause imaging orders until biomarker data is available which requires around 15 min delay. When biomarker data is available, these are printed and provided timely to the provider along with the cut-off for an elevated test. The cut-off used are 65 pg./mL for GFAP and 360 pg./mL for UCH-L1. The provider will also be handed a refresher education on the published data on the negative predictive value (NPV) and positive predictive value (PPV) of the test. The decision whether to pursue a CT of the head will be left to the provider and patient discussion considering the biomarker data. A test is considered non-elevated only if both biomarkers were below the pre-defined cut-off.

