### Safety analysis

Safety analysis will be evaluated by assessing the rate of delayed diagnosis of significant intracranial findings that require intervention and will be compared between the two groups using a Pearson’s Chi-squared test. The time to CT head imaging will also be compared between two groups using a two-sample *t*-test or Wilcoxon rank sum test depending on the normality assumption.

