### Secondary analyses

Relevant secondary analyses reported in Table 2 will be studies as described below:

Assess the impact of biomarker result access on physician decision-making for CT use (Time to obtaining CT head, *t*-test).Hospital Length of stay in published versus blinded group (*t*-test).Hospital costs for published versus blinded group (Incremental cost effectiveness analysis).GCS and GOS-E comparison in published versus blinded groups at 6 and 12 months (Ordinal logistic regressions).Compare rates of discharge, floor admission, and ICU admission between the published and blinded groups (logistic regression for each outcome, taking admission GCS and age as covariates).Within all patients, define the sensitivity and specificity for predicting GOS-E scores at 6 and 12 months for biomarker test as well as when combined with clinical variables and BIG criteria (ROC analysis).Within the published group, study predictors of adherence to biomarker-based guidelines among providers (logistic regression).

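### Time to head CT is compared only among scanned patients, a group the intervention is meant to change, so a case-mix difference can look like faster or slower imaging

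*Protocol article*

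**What the plan says.** In the protocol article, Safety analysis states: "The time to CT head imaging will also be compared between two groups using a two-sample" t-test or a Wilcoxon rank sum test, depending on normality. Secondary analyses lists "Time to obtaining CT head", with a t-test, as the measure of how access to results affects physicians' CT decisions. Neither section gives a value, rank, censoring rule or competing event for a patient who never has a CT.

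Table 2 (Study objective) has two relevant rows. The clinical decision-making row takes CT timing and provider rationale as its outcome. A separate row reads "Compare time from triage to CT decision between arms", with the purpose "Evaluate whether biomarker access accelerates or delays decision-making".

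Three sections bear on when a CT may take place:

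- Pre-randomization procedures: on enrolment, providers are "requested to hold off on obtaining CT head imaging until randomization and biomarker data is available", with no distinction by arm.
- Procedures for blinded biomarker arm: "no further changes are requested from the provider".
- Procedures for the published biomarker arm: "providers are requested to pause imaging orders until biomarker data is available which requires around 15 min delay".

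**The concern.** A time to CT exists only for a patient who had one. Post-randomization in-hospital assessment records after allocation whether a CT was done and when, and Table 3 lists head CT as conditional on being performed. Whether a patient is scanned is the primary endpoint. The trial's hypothesis is that disclosure lowers it, and in the published arm the decision is made with the biomarker result in view. Comparing times among scanned patients therefore conditions on an outcome that the intervention is designed to change. The more the trial succeeds on its primary endpoint, the less alike the two scanned groups become.

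The comparison is given two uses: it stands under safety, and it is the stated analysis of physician decision-making. Rationale for randomization relies on allocation for unbiased estimation and an intention-to-treat analysis. This comparison has neither, so it could report acceleration or delay when no patient's timing had changed.

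**Working it through.** The plan states no figure for time to CT, so there is none to reproduce. The CT rates and arm size come from Sample size justification. All timings below are assumptions.

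**1. Who enters the test.** The baseline CT rate is 70%, with a 15% reduction. Read as percentage points, the published rate is 55%; read as relative, it is 0.70 × 0.85 = 59.5%. With 150 evaluable per arm, the percentage-point reading gives:

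- blinded: 150 × 0.70 = 105 scanned, 30% left out
- published: 150 × 0.55 = 82.5 scanned, 45% left out

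With 175 per arm the counts are 122.5 and 96.25.

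**2. How far the scanned groups differ.** Suppose that disclosure only averts scans. Then 55% of patients would be scanned in either arm, 15% only in the blinded arm, and 30% in neither. The averted type makes up 15/70 = 21.4% of scanned blinded-arm patients and none of the scanned published-arm patients.

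Let D be how much later, on average, the averted type is scanned than the patients scanned in either arm. If no individual's timing changes,

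difference in means (published − blinded) = −(15/70) × D.

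The rejection rates come from 4,000 simulated trials for each D, with 150 per arm, an assumed SD of 40 min and a nominal level of 5%.

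| Assumed D (min) | Spurious difference (min) | t-test rejects | Wilcoxon rejects |
|---|---|---|---|
| 0 | 0 | 5% | 5% |
| 15 | −3.2 | 8% | 8% |
| 30 | −6.4 | 18% | 17% |
| 60 | −12.9 | 49% | 42% |

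If D is negative, the sign reverses and the artefact looks like delay. Under the relative reading the multiplier is 10.5/70 = 0.15, so D = 30 gives 4.5 min.

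**3. The same effect through case-mix.** Assume that 40% of patients are high-risk and scanned at 40 min, and that the other 60% are scanned at 90 min, in both arms. Assume CT rates of 90% and 57% (blinded) and 85% and 35% (published).

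- Blinded: 0.40 × 0.90 = 0.36 and 0.60 × 0.57 = 0.342, total 0.702. Mean time = (0.36 × 40 + 0.342 × 90)/0.702 = 45.18/0.702 = 64.4 min.
- Published: 0.40 × 0.85 = 0.34 and 0.60 × 0.35 = 0.21, total 0.55. Mean time = (0.34 × 40 + 0.21 × 90)/0.55 = 32.5/0.55 = 59.1 min.

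This is an apparent acceleration of about 5 min with no change in timing within either risk group.

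**4. What an all-patient analysis measures.** Take the example in step 3 over an assumed 240-minute horizon, counting never-scanned patients as CT-free throughout.

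- Blinded: 240 − 0.36 × 200 − 0.342 × 150 = 116.7 CT-free minutes.
- Published: 240 − 0.34 × 200 − 0.21 × 150 = 140.5 CT-free minutes.

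The difference of 23.8 min comes wholly from the lower CT rate. The contrast is protected by randomisation, but it does not measure decision speed.

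**5. The request to hold CT.** Pre-randomization procedures makes the request for every enrolled patient and names both randomisation and the biomarker result as its end. The blinded-arm section, which follows, asks for nothing further; this can mean nothing beyond the hold already requested, or no hold. The published-arm section states a pause of about 15 min. On one reading both arms wait for the assay; on the other only the published arm does. The meaning of any time difference depends on which applies.

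**The case against.** The strongest reply is that the article nowhere restricts the comparison to scanned patients, and that a condensed article may leave the handling of the others to a fuller document. A Wilcoxon test could include everyone if unscanned patients took the worst rank. But no such rule is given, and Secondary analyses names only a t-test, which needs an observed time. The tests are fixed in the text, so the point stands.

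It is also fair that the size is unknown. The risk shares, scan times and SD used above are not in the documents, and the eligibility criteria exclude patients judged too high-risk to wait for the assay. This limits the claim to a risk. The endpoint is one of many secondary comparisons, delayed diagnosis is the first-named safety measure, and the primary analysis is unaffected.

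Four stronger readings are tempting but not supported:

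- That the analysis contradicts Table 2. The clinical decision-making row has CT timing as its outcome, and Secondary analyses matches it. The triage-to-decision row is a separate objective with no test named in the article, which may be left to the SAP.
- That triage-to-decision time is already available for every patient. No section says that the time of a decision not to scan is recorded.
- That the protocol imposes a 15-minute delay on the published arm alone. The wording is ambiguous, and even a one-arm pause would be a real part of the strategy under test, not a spurious shift.
- That naming a t-test or Wilcoxon in one section and only a t-test in the other is a material conflict. The second is a shorthand list.

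**Conclusion.** The concern holds as a risk to interpretation. The planned comparison of time to CT can, as written, use only scanned patients, about 70% of one arm and 55% of the other at the planning rates. Those groups are formed by the primary endpoint, so randomisation does not make them comparable.

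Under the assumption that disclosure only averts scans, the shift is 21.4% of the timing gap D. For assumed gaps of 15 to 60 min it is 3.2 to 12.9 min, with t-test false-positive rates of about 8% to 49% at 150 per arm and an SD of 40 min. At D = 0 there is no bias, and a negative D reverses the sign. A reader might infer that the trial's timing result will be biased towards acceleration; the documents do not support that, because they give no timings by patient type. What they do support is that this comparison should not serve as between-arm evidence on safety or decision speed.

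**What to change.** 1. In Safety analysis and Secondary analyses, label the time-to-CT comparison among scanned patients as descriptive, and do not use it as between-arm evidence on safety or decision speed.
2. For a randomised comparison, analyse all randomised patients from randomisation by cumulative incidence of head CT, with ED departure without CT as a competing event. State that the result reflects CT rate and timing together and does not isolate decision speed.
3. For decision speed, use the Table 2 triage-to-decision time in all patients. This requires recording the time of a decision not to scan.
4. Reconcile Pre-randomization procedures and the two arm-specific procedure sections on whether the request to hold CT until the biomarker result applies to both arms, and interpret time outcomes accordingly.

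Items 1, 2 and 4 are changes of wording. CT timing is already collected, and ED departure can probably be derived from the recorded length of stay. Item 3 may need one added data field. No extra patients or visits are needed.

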### Secondary analyses

Relevant secondary analyses reported in Table 2 will be studies as described below:

Assess the impact of biomarker result access on physician decision-making for CT use (Time to obtaining CT head, *t*-test).Hospital Length of stay in published versus blinded group (*t*-test).Hospital costs for published versus blinded group (Incremental cost effectiveness analysis).GCS and GOS-E comparison in published versus blinded groups at 6 and 12 months (Ordinal logistic regressions).Compare rates of discharge, floor admission, and ICU admission between the published and blinded groups (logistic regression for each outcome, taking admission GCS and age as covariates).Within all patients, define the sensitivity and specificity for predicting GOS-E scores at 6 and 12 months for biomarker test as well as when combined with clinical variables and BIG criteria (ROC analysis).Within the published group, study predictors of adherence to biomarker-based guidelines among providers (logistic regression).

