## Methods and analysis

### Study objective

The BRAIN-CT trial investigates whether providing emergency-department clinicians with rapid GFAP and UCH-L1 results, via the point-of-care i-STAT TBI cartridge, changes imaging behavior in adults with mild traumatic brain injury. The primary objective (Table 2) is to compare the proportion of patients who receive a head CT scan between a biomarker-published arm and a standard-care (biomarker-blinded) arm; we hypothesize that real-time access to GFAP and UCH-L1 levels will lower the CT scan rate compared with standard management. To address this objective, we have designed a prospective, randomized, open-label, blinded-endpoint (PROBE) adaptive trial that will enroll 350 participants, randomized 1:1 to biomarker-published versus biomarker-blinded arms using permuted blocks stratified by age group, biological sex, race, and baseline Canadian CT Head Rule risk category (Supplementary Table 1). Frequent interim analyses with prespecified efficacy and futility boundaries will permit early stopping if criteria are met.

**Table 2 tab2:** Primary and secondary objectives of the BRAIN-CT trial.

Objective	Category	Objective description	Outcome measured
Primary	–	Evaluate whether real-time access to point-of-care TBI biomarker results (GFAP, UCH-L1) reduces the use of cranial CT imaging.	Proportion of patients undergoing head CT.
Secondary (clinical impact) two-arm comparisons	Clinical decision-making	Assess the impact of biomarker result access on physician decision-making for CT use.	CT imaging timing and provider rationale.
	Efficiency and cost	Determine whether biomarker use reduces ED/hospital length of stay and healthcare costs.	LOS, resource use, hospital charges. Perform a formal ICEA of biomarker testing versus standard care.
	Patient outcomes	Compare short-term outcomes between arms (neurological deterioration, readmissions, GOS, GCS).	GOS-E/GCS at 6 months and 1-year follow-up, neurological symptoms.
	Radiation exposure	Quantify radiation dose reduction per patient between arms.	Directly measure a key safety benefit.
	Disparity analysis	Identify patient subgroups (e.g., by age, injury mechanism, comorbidity) where biomarkers influence decision-making.	Stratified CT usage, subgroup analysis of impact.
	Safety monitoring	Monitor for adverse outcomes from missed injuries in biomarker-guided arm.	Adverse events, unexpected deterioration, delayed diagnoses.

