### Post-discharge follow-up

Study staff will conduct structured telephone interviews at 6 months and 12 months after the ED visit to ascertain persistent or late-presenting neurologic symptoms, unplanned healthcare utilization (ED visits, hospital readmissions, outpatient imaging), and any delayed diagnoses of intracranial injury. Future contact is approved by subjects at the time of consent. When participants cannot be reached after three call attempts, electronic health-record review and contact of designated surrogates are attempted to complete the data set. Designated surrogates are individuals determined by the subject to be their emergency contact for the study for future contact and are named at the time of informed consent.

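### The between-arm comparison of GCS at 6 and 12 months cannot be carried out by the telephone follow-up described, and would have almost nothing to estimate if it could

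*Protocol article*

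**What the plan says.** Three parts of the protocol article bear on this.

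- **Outcome.** In Table 2 (Study objective), the Patient outcomes row has the objective "Compare short-term outcomes between arms (neurological deterioration, readmissions, GOS, GCS"). Its outcome column reads "GOS-E/GCS at 6 months and 1-year follow-up, neurological symptoms".
- **Analysis.** The Secondary analyses section lists "GCS and GOS-E comparison in published versus blinded groups at 6 and 12 months (Ordinal logistic regressions"). A separate item in that section uses GOS-E at the same two times in an ROC analysis.
- **Data collection.** The Post-discharge follow-up section says: "Study staff will conduct structured telephone interviews at 6 months and 12 months after the ED visit to ascertain persistent or late-presenting neurologic symptoms". The rest of the stated call content is "unplanned healthcare utilization (ED visits, hospital readmissions, outpatient imaging), and any delayed diagnoses of intracranial injury". If calls fail, "When participants cannot be reached after three call attempts, electronic health-record review and contact of designated surrogates are attempted to complete the data set".

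The schedule in Table 3 marks both follow-up contacts as phone contacts and names no instrument for either. GCS appears there only in the baseline assessment at enrolment. The article describes no in-person visit after discharge.

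**The concern.** A planned endpoint has to be obtainable by the planned method of assessment. GCS combines eye opening, verbal response and motor response, and an examiner scores it at the bedside. A caller cannot observe eye opening or motor response, and a surrogate's account does not replace the examination. A health record would hold a GCS near 6 or 12 months only for a patient who happened to be seen for some acute reason, which is a selected group.

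The scale also suits this time point poorly. It grades depth of impaired consciousness, and the trial enrols only patients in its top three points. Someone who can complete a structured interview months later would be expected to be at the ceiling.

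At stake is a named secondary outcome with a fixed analysis method. Followed literally, it would yield either missing data or a column of nearly identical values. If the latter were reported as no difference between arms, it could be mistaken for evidence on patient outcomes, although it would carry almost none.

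**Working it through.** The article gives no figure to reproduce. The check sets the sections side by side and then asks what the model could estimate.

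**Step 1: required against collected.**

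| Item at 6 and 12 months | Required by | Named in the call content or Table 3 follow-up rows? | Obtainable by telephone or surrogate? |
|---|---|---|---|
| GCS | Table 2; Secondary analyses | No | No, needs direct examination |
| GOS-E | Table 2; Secondary analyses (two items) | No | Yes, scored by questioning |
| Neurologic symptoms | Table 2 | Yes, call content | Yes |
| Readmissions | Table 2 | Yes, call content | Yes |

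GCS is the only row where the stated mode of follow-up rules the measurement out. For GOS-E the article is silent on the instrument, but the mode fits.

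**Step 2: what the ordinal model needs.** With K observed outcome categories, the proportional-odds model is

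logit P(Y ≤ k) = α_k − β × arm, for k = 1, …, K − 1.

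If every participant scores 15, then K = 1. There are K − 1 = 0 cumulative logits, the likelihood does not depend on β, and the arm effect is not estimable at any sample size.

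**Step 3: sensitivity to the ceiling assumption.** The documents give no GCS distribution at follow-up, so the number m scoring below 15 is varied here purely as an illustration. Take the 300 evaluable patients of the Sample size justification (150 per arm), all assessed, which is favourable. Split m equally between arms and group scores as below 15 against 15. Then

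var(log OR) = 2 × [1/(m/2) + 1/(150 − m/2)],

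and the 95% interval around an odds ratio of 1 is exp(±1.96 × SE).

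| Assumed m of 300 | Variance | SE | 95% interval around OR = 1 |
|---|---|---|---|
| 0 | not defined | – | not estimable |
| 2 (0.7%) | 2 × (1/1 + 1/149) = 2.013 | 1.419 | 0.06 to 16.1 |
| 6 (2%) | 2 × (1/3 + 1/147) = 0.680 | 0.825 | 0.20 to 5.0 |
| 30 (10%) | 2 × (1/15 + 1/135) = 0.148 | 0.385 | 0.47 to 2.1 |

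For the small values of m that seem plausible, the interval is too wide to inform. The last row shows that the comparison would stay imprecise even if one patient in ten were below 15. These are large-sample approximations, and they are crude for the smallest m. Step 1 does not depend on them.

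**The case against.** The strongest reply is that this is a condensed article. The interview form belongs in the full protocol, the call is described as structured, and Table 2 and the Secondary analyses section both say what is measured at 6 and 12 months. Its absence from the follow-up section would then be only brevity.

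For GOS-E this reply stands. A reader might infer that GOS-E will not be in the data, so that the patient-outcome and outcome-prediction objectives cannot be answered. The documents do not support that:

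- GOS-E is obtained by questioning the patient or a proxy, and a structured telephone interview can carry it.
- The fallback includes surrogates designated at consent as well as record review.
- The Patient outcomes objective also covers deterioration, symptoms and readmissions. The in-hospital and post-discharge sections collect these.
- The Outcome prediction row of Table 2 allows alternatives: "Correlation with GOSE score, readmission, or symptom progression".

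The dependence on GOS-E should not be overcounted either. In the Secondary analyses section it covers two items: the arm comparison, and one ROC item that includes the combination with BIG criteria.

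For GCS the reply fails. No interview form or analysis plan can make a bedside examination scorable by telephone, and the article describes no visit at which it could be done.

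A second reply is that the ceiling at 15 is a judgement. It is, and it is treated here as an assumption. The finding on obtainability does not need it.

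A third is that GOS against GOS-E in Table 2 is editorial. That is fair: no analysis uses GOS, and the same row's outcome column says GOS-E.

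**Conclusion.** The comparison of GCS between arms at 6 and 12 months is wrong as planned. The follow-up described cannot produce the measurement, and if values were recorded they would be expected to sit almost entirely at 15.

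The first conclusion rests on the article's own description of follow-up and on how GCS is scored. The second rests on the assumption that survivors of a GCS 13–15 cohort are nearly all at the ceiling months later.

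The size is limited: one of the two scales in one of the seven listed secondary analyses. The primary endpoint (proportion undergoing head CT), the safety analysis and the sample size are unaffected. The GOS-E objectives are not shown to be unanswerable; there the article only needs to be clearer. It is still worth correcting before follow-up calls begin, because a 6-month assessment that is missed or taken on the wrong scale cannot be recovered.

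**What to change.** 1. Remove GCS from the 6- and 12-month outcomes in the Patient outcomes row of Table 2 and from the matching item in Secondary analyses. Keep it as a baseline and in-hospital measure.
2. Make GOS-E the sole ordinal functional outcome at 6 and 12 months. Adjust its ordinal model for the randomisation factors, which are already collected and for which the primary logistic model already adjusts. The covariate list may sit in the analysis plan.
3. As a clarification rather than a separate defect, name GOS-E, answered by the patient or the designated surrogate, in the Post-discharge follow-up section and in the two follow-up rows of Table 3. Replace GOS with GOS-E in the objective wording of Table 2.

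The cost is a few wording changes. If GOS-E is not already on the interview form, it adds a few minutes to calls already planned. No visit, participant or change to the primary analysis is needed.

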### Study design and methods

The BRAIN-CT trial is a single-center prospective, randomized, open-label, blinded endpoint study conducted in the ED of Grady Memorial Hospital, a level I trauma center. After completion of initial screening, 350 adults aged 18–85 years will be randomized 1:1 to either a biomarker-published arm (real-time GFAP and UCH-L1 values released to clinicians coupled to education on biomarker data) or a biomarker-blinded arm (standard care without biomarker disclosure). The study flow chart is provided in Figure 1. Allocation uses computer-generated permuted blocks stratified by age (3 Strata: 18–30, 31–50, 51–85 years), biological sex, race (2 Strata: Black, Not Black), Glascow Coma Scale (GCS) (2 Strata: 15, 13–14) and baseline Canadian CT Head Rule risk category (3 Strata: High Risk, Medium Risk, None) to balance key factors in routine decision making. The maximum sample size remains 350 participants for the initially planned cohort. Outcome adjudicators are masked to treatment assignments. Given the pre-existing FDA-approval of the use of the TBI biomarker testing in mild-TBI, the study is deemed no more than minimal risk to participants and a data safety and monitoring board was not required. This study is registered with clinicaltrials.gov (Identifier: NCT06932588), and the study was approved by the Institutional Review Board at Emory University and the Research Oversight Committee at Grady Memorial Hospital.

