### Primary efficacy analysis

The primary endpoint is the proportion of patients undergoing a head CT scan which will be reported as percentage of total patients. The key hypothesis:

H_0_ (null): There is no difference in CT head scan rates between the published biomarker and blinded biomarker arms.H_1_ (alternative): The published biomarker arm has a significantly lower CT scan rate compared to the blinded biomarker arm.

To evaluate the hypothesis, we will perform univariate analysis using a Pearson’s chi-square test followed by a pre-specified logistic regression model that adjusts for stratification/randomization variables (e.g., site, age, GCS score category), providing an adjusted odds ratio (aOR) and 95% confidence interval (CI). A statistically significant result will be defined with a two-tailed *p*-value of less than 0.05, or adjusted odds ratios for predicting CT head acquisition with a 95% confidence interval below 1.0. In the event the *p*-value approaches the significance threshold (e.g., p between 0.05 and 0.10), results will be interpreted with caution, and effect size estimates will be emphasized to assess the practical impact of the observed differences.

For subgroup analysis across randomization strata, we will use the same testing as primary hypothesis. Then, we will formally test for heterogeneity of treatment effect using interaction terms in the logistic regression models. A *p* < 0.05 for the interaction will be considered evidence of differential efficacy across subgroups (given the exploratory nature of interaction testing).

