### Rationale for randomization

Randomization ensures that known and unknown confounders–such as injury mechanism, clinician decision-making patterns, and patient comorbidities–are evenly distributed between the biomarker-published and biomarker-blinded arms, thereby allowing unbiased estimation of the causal effect of real-time biomarker disclosure on head-CT utilization. Stratification by age, biological sex, race, GCS score and Canadian CT Head Rule risk category further improves balance across prognostic variables. Randomization is essential in this trial because CT decisions are inherently subjective, and without allocation concealment, selection bias or preferential imaging decisions could distort observed differences. The 1:1 parallel-group design also facilitates straightforward intention-to-treat analysis and preserves statistical validity in interim monitoring.

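### Hospital length of stay is compared by a plain t-test that ignores the five randomisation factors; if those factors are prognostic, the test is conservative and loses some power (minor)

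*Protocol article*

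**What the plan says.** **Allocation.** Study design and methods stratifies permuted blocks by five factors: age (3 levels), sex (2), race (2), GCS (2) and Canadian CT Head Rule category (3). The stated purpose is "to balance key factors in routine decision making". Rationale for randomization adds: "Stratification by age, biological sex, race, GCS score and Canadian CT Head Rule risk category further improves balance across prognostic variables".

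**Primary outcome.** After the chi-square test, the Primary efficacy analysis section fits a "pre-specified logistic regression model that adjusts for stratification/randomization variables (e.g., site, age, GCS score category" and further such variables, since the list is given by example.

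**Secondary outcomes (Secondary analyses).**
- Length of stay: "Hospital Length of stay in published versus blinded group", with a t-test as the method. A t-test takes no covariates.
- Discharge, floor admission and ICU admission: "logistic regression for each outcome, taking admission GCS and age as covariates". Sex, race and Head Rule category are absent.
- Function: "GCS and GOS-E comparison in published versus blinded groups at 6 and 12 months", with ordinal logistic regression named and nothing said about covariates.

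**The concern.** Blocking within strata makes the two arms more alike on the stratification factors than simple randomisation would. If those factors predict the outcome, the difference in means varies less from trial to trial than the ordinary t-test assumes. The t-test still charges for between-stratum variation that the design has largely removed. Its interval is then too wide, its true type I error is under 5%, and a real difference is more likely to be missed.

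Length of stay carries the efficiency objective in Table 2. All five factors are recorded before randomisation, so the plan has the data to recover the lost precision. It already does so for the primary outcome.

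**Working it through.** **Is there a plan figure to reproduce?** Not for this point. The only power statement (Sample size justification: 300 evaluable, 150 per arm, at least 80%) concerns the CT rate. No effect size, standard deviation or power is given for length of stay. The 80% below is borrowed as a reference level only.

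**Inputs.** From the article: 1:1 allocation, 350 enrolled, two-sided 5% level, and 3 × 2 × 2 × 2 × 3 = 72 strata, so 350/72 = 4.9 patients per stratum on average. Assumed: the share R² of outcome variance explained by the five factors, the stratum frequencies, the block size and the effect size.

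**Closed form, with the outcome SD set to 1.**
- Standard error reported by the t-test: 2/√n. For n = 350 this is 2/18.71 = 0.107.
- True SD of the difference if the factors were perfectly balanced: (2/√n)·√(1 − R²). At R² = 0.20 this is 0.107 × 0.894 = 0.096.
- True type I error of the t-test: 2·[1 − Φ(1.96/√(1 − R²))].
- For an effect with nominal 80% power (1.96 + 0.8416 = 2.8016 standard errors), t-test power is Φ(0.8416/√(1 − R²)).
- Power of the adjusted model is Φ(2.8016/√(1 − R²) − 1.96).

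| R² | t-test type I error | t-test power | Adjusted power | Gain (points) |
|---|---|---|---|---|
| 0.02 | 4.8% | 80.2% | 80.8% | 0.6 |
| 0.05 | 4.4% | 80.6% | 82.0% | 1.4 |
| 0.10 | 3.9% | 81.3% | 84.0% | 2.7 |
| 0.15 | 3.4% | 81.9% | 86.0% | 4.0 |
| 0.20 | 2.8% | 82.7% | 88.0% | 5.3 |
| 0.30 | 1.9% | 84.3% | 91.8% | 7.5 |

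Perfect balance is a limit. With 72 small strata, incomplete blocks leave some imbalance.

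**Simulation of the stratified design** (n = 350, effect 0.3 SD, blocks of 2 and 4, 2,000 trials per setting, assumed stratum frequencies):

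| R² | t-test SE | True SD (null) | t-test type I error | Power, t-test → adjusted (blocks of 2; 4) |
|---|---|---|---|---|
| 0.10 | 0.107 | 0.101–0.103 | 3.9–4.5% | 81.2 → 84.2%; 81.4 → 83.6% |
| 0.20 | 0.107 | 0.097–0.099 | 3.5–3.7% | 82.6 → 87.7%; 81.8 → 88.2% |
| 0.30 | 0.107 | 0.092–0.093 | about 2.1% | 83.7 → 92.0%; 82.8 → 92.0% |

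The adjusted model held 4.6% to 5.5% in these settings. A further simulation at n = 300 gave gains of 0 to 0.5 points at R² = 0.02. At R² = 0.05 it gave 1.3 to 1.9 points, with t-test type I error of 4.8% to 5.2%, so no visible conservatism.

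**Disposition** (n = 350, logistic models; age and GCS against all five factors, factor strengths assumed):
- Weak factors: no visible difference.
- Moderate factors: reported SE 0.232 against a true SD of 0.225–0.229; type I error 4.2–4.6%; power about 80% → 81%.
- Strong factors: reported SE 0.237 against 0.224–0.228; type I error 3.7–4.0%; power about 68% → 73%.

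In the strong case, full adjustment raises the standard error of the log odds ratio from 0.237 to 0.257 (null runs). With a true effect, the mean estimate moves away from zero, from −0.607 to −0.705. Power rises because the estimate grows by more than its standard error.

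**The case against.** **The size is hypothetical.** The article calls the factors prognostic but not how strongly, or for which outcome, and it describes them mainly as drivers of imaging decisions. With an R² of 0.05 or less for length of stay, the change is barely visible. This stands, and it is why the size is given as a range.

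**The planned test is safe.** An unadjusted t-test after stratified randomisation does not inflate false positives, these are secondary outcomes, and the primary outcome has its adjusted model. This also stands and sets the severity.

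**Two prespecified covariates for disposition are legitimate.** Largely true: with age and GCS already in the model, little remains to be gained. Disposition is therefore only an addition to the point.

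**Stronger readings that the documents do not support:**
- *GOS-E is wrongly left unadjusted.* The article names a model family and is silent on covariates, which a condensed article may leave to the full plan. Silence is not an unadjusted analysis.
- *Adjustment would shorten every interval.* That holds for the linear model. In logistic or ordinal models, adding prognostic covariates does not narrow the log-odds-ratio interval, as the disposition figures show.
- *A 5-point gain needs an R² of only about 0.13.* That sets adjusted power against a flat 80%. Under stratification the t-test already reaches 81% to 83%, so a 5-point gain needs an R² nearer 0.20.

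What remains is not an argument from silence: the t-test and the two-covariate list are stated choices.

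**Conclusion.** The point holds for length of stay and is minor. The plan stratifies by five factors that it calls prognostic, adjusts the primary model for them, and then specifies a test for length of stay that cannot use them. If they predict length of stay, the standard error is too large, the true level is below 5%, and about 1 to 2 points of power are lost at R² = 0.05, or about 3 to 9 points at R² = 0.10 to 0.30. If they do not, almost nothing is lost. These figures rest on an assumed R², assumed stratum frequencies and block sizes, and a reference power of about 80% that the article does not claim for this outcome. For disposition the loss is about 0 to 5 points. GOS-E is not part of the finding.

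**What to change.** In Secondary analyses, replace the length-of-stay t-test with a linear model on a suitable scale (for example log), with arm and the main effects of age group, sex, race, GCS category and Canadian CT Head Rule category. Use main effects rather than stratum indicators, because 72 cells would hold about 4.9 patients each.

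As a minor addition, extend the disposition logistic models by at least the Head Rule category, and by sex and race where event counts allow. For a sparse outcome such as ICU admission, use a penalised fit or leave out race and sex first.

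The cost is a change of wording; no new data are needed. On a log scale the length-of-stay effect becomes a ratio of geometric means and must be reported as such. The disposition odds ratios become conditional on more factors, and their intervals should not be expected to narrow.
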